## Abstract

**Background:**

Early intervention services for psychotic disorders optimally interlock strategies to deliver: (i) Early Detection (ED) to shorten the time between onset of psychotic symptoms and effective treatment (i.e. Duration of Untreated Psychosis, DUP); and (ii) comprehensive intervention during the subsequent 2 to 5 years. In the latter category, are teams (‘First-episode Services’ or FES) that integrate several empirically supported treatments and adapt their delivery to younger patients and caregivers. There is an urgent need to hasten access to established FES in the U.S. Despite improved outcomes for those in treatment, these FES routinely engage patients a year or more after psychosis onset. The Scandinavian TIPS study was able to effectively reduce DUP in a defined geographic catchment. The guiding questions for this study are: can a U.S. adaptation of the TIPS approach to ED substantially reduce DUP and improve outcomes beyond existing FES?

**Methods/Design:**

The primary aim is to determine whether ED can reduce DUP in the US, as compared to usual detection. ED will be implemented by one FES (STEP) based in southern Connecticut, and usual detection efforts will continue at a comparable FES (PREP^R^) serving the greater Boston metropolitan area. The secondary aim is to determine whether DUP reduction can improve presentation, engagement and early outcomes in FES care. A quasi-experimental design will compare the impact of ED on DUP at STEP compared to PREP^R^ over 3 successive campaign years. The campaign will deploy 3 components that seek to transform pathways to care in 8 towns surrounding STEP. Social marketing approaches will inform a public education campaign to enable rapid and effective help-seeking behavior. Professional outreach and detailing to a wide variety of care providers, including those in the healthcare, educational and judicial sectors, will facilitate rapid redirection of appropriate patients to STEP. Finally, performance improvement measures within STEP will hasten engagement upon referral.

**Discussion:**

STEP-ED will test an ED campaign adapted to heterogeneous U.S. pathways to care while also improving our understanding of these pathways and their impact on early outcomes.

**Trial registration:**

ClinicalTrials.gov: NCT02069925. Registered 20 February 2014.

## Background

### The promise of early detection

Psychotic disorders are a source of severe distress, disability and economic cost under usual systems of care. The prototypic schizophrenia spectrum disorders affect between 0.55% and 1% of people during their lives [1]; and typically manifest as a ‘first-episode’ of psychotic symptoms in adolescence or early adulthood. This is an especially formative period for social and vocational trajectories and psychotic disorders are among the top 20 causes worldwide of years lived with disability (YLD), exceeding epilepsy, ischemic heart disease and Alzheimer’s disease in their impact amongst the chronically ill [2]. With routine care, less than one-fifth of patients achieve full recovery after a first episode of psychosis [3] and less than one-third achieve minimal age-appropriate employment or education [4]. Chronic psychotic disorders, while relatively less prevalent, lead annual U.S. expenditures on mental illnesses, with $22.7 billion in direct healthcare costs, and $32.4 billion in indirect costs stemming from unemployment, reduced workplace productivity, premature mortality from suicide, and family caregiving [5].

Early intervention can significantly ameliorate the poor outcomes of usual care. The first 2–5 years after psychosis onset presage much of the eventual clinical and psychosocial deterioration in schizophrenia spectrum disorders [6] including one-third of completed suicides [7], relapse and re-hospitalizations [8], violence [9] and neurocognitive dysfunction [10]. This period also offers the opportunity to modify several prognostic factors including substance misuse, social isolation, negative symptoms and cognitive dysfunction [11]. These factors can derail an already vulnerable period of emerging adulthood [12]. Relapses in the first year or two after the first episode, and accumulated duration of positive symptoms of psychosis in the first few years of illness are associated with worse neurocognition 5–10 years later [13]. The hypothesis of a ‘critical period’, wherein secondary prevention efforts 2–5 years after psychosis onset might disproportionately leverage long term functional gains, [14] has stimulated a rich variety of approaches to early intervention.

Early Intervention (EI) for psychotic disorders can be conceptualized as including interlocking strategies to deliver: (i) Early Detection (ED) to shorten the time between onset of psychotic symptoms and effective treatment (i.e. Duration of Untreated Psychosis, DUP); and (ii) comprehensive intervention during the 2 to 5 years after identification of a psychotic disorder [15]. Of particular promise, in the latter category, are teams (henceforth ‘First-episode Services’ or FES) that integrate several empirically supported treatments and adapt their delivery to younger patients and their caregivers. FES have demonstrated improvements in symptoms, functioning and costs in a range of healthcare systems [16,17]. The two collaborating FES in this project (clinic for Specialized Treatment Early in Psychosis, or STEP in New Haven and Prevention and Recovery in Early Psychosis, or PREP^R^ in Boston) have successfully applied comparable FES in similar settings to deliver feasible, sustainable and effective care [18,19]. STEP recently completed the first U.S. randomized controlled trial to determine the feasibility and effectiveness of this public-sector based approach to FES [18]. This trial has also collected detailed information on sources of direct and indirect cost [20–22] that support international data on the health economic benefits of FES.

There is an urgent need to hasten access to FES in the U.S. Despite improving outcomes for those in treatment, STEP and PREP^R^ continue to admit patients long after psychosis onset. For example, over half (51%) of all entrants to STEP over the past 6 years had endured a DUP longer than 3 months with evidence of significant morbidity on arrival to the service: about 10% of entrants had already attempted suicide, 45% had a co-morbid substance use disorder and 60% had dropped out of school or employment while 90% entered care after a behavioral crisis requiring hospitalization [23]. The same proportion (50%) had endured a similarly prolonged DUP over the past 5 years at PREP^R^.

Early Detection has the potential to substantially reduce DUP and extend the impact of existing FES. The largest experimental study of ED has been the TIPS study. TIPS delivered a combination of public and targeted education campaigns coupled with rapid availability of FES in 2 healthcare sectors in Norway, whereas two control sectors (in Norway and Denmark) delivered comparable FES without the benefit of these efforts to reduce DUP. This strategy more than halved DUP (from a median of 15 to 4.5 weeks) [24] at the ED sites. This DUP reduction was tied to markedly reduced distress and disability at clinical presentation, including reduced positive and negative symptoms of psychosis [24] and suicidal behavior [25]; persistently improved negative symptoms at 5 years [26] and resulted in twice the rate of recovery (31 vs. 15%) at 10 years [27]. Notably, when the information campaign was interrupted due to lack of continued funding, this resulted in a decay of the DUP toward the control levels followed by attendant worsening in outcomes [28]. This validated a causal role for DUP in affecting outcomes rather than functioning solely as a marker of poor prognosis subgroups [29]. Although one other study in Singapore used a similarly broad, multifocal campaign to reduce DUP and improve pathways to care, [30] other less comprehensive attempts have failed to reduce DUP [31], demonstrating the challenge of replicating the promising findings from TIPS.

Several factors argue for careful study rather than straightforward application of the TIPS approach to U.S. settings. Pathways to specialty care in the U.S. are diverse, potentially weakening some but also magnifying the impact of other efforts toward early detection. Also, the anticipated but unclear changes in U.S. pathways over time (e.g. with ongoing reforms in access to health insurance [22]) make it vital to test any ED strategy against a control setting to disentangle the effects of an ED campaign from secular changes in the U.S. healthcare environment. Finally, FES care is a rarity in most U.S. settings and can reduce DUP in a region simply by its presence. Controlling for this effect across 2 established FES can a) help disentangle the impact on DUP of a distinct ED campaign and, b) if the ED campaign is successful, clarify the added value of optimizing timing (ED) over already existing efforts to improve the quality of early treatment (i.e. FES).

### Contextualizing early detection within pathways to care

Our attempt to reduce DUP in the complex U.S. healthcare environment uses a model (Figure 1) that (a) incorporates local knowledge and uncertainty of the size and determinants of various sources of delay and (b) the pathways to care that reveal potentially malleable nodes on which to prioritize efforts. We prefer to categorize the determinants of DUP as including a ‘demand’ side (e.g. delays in effective help-seeking resulting from factors including delays in illness identification and delayed attempts to access healthcare by patients and caregivers) [32] and a ‘supply’ side (delays by professionals in initiating treatment that include delays in diagnosing and initiating or referring to appropriate treatment). Given the variability of impact of sources of delay across various U.S. settings, our approach is agnostic on whether to prioritize demand or supply side interventions. We begin with the premise that deploying interventions targeting these two domains of DUP with already demonstrated success (in the TIPS project) provides an empirically tractable basis for the main goal of DUP reduction while also allowing for vital information to be collected on determinants of DUP within the context of local pathways to care.

**Figure 1 Fig1:**
[figure not shown]
**Heuristic model for DUP in STEP’s catchment.**

Pathways to care can be defined as “the sequence of contacts with individuals and organizations prompted by the distressed person’s efforts, and those of his or her significant others, to seek help as well as the help that is supplied in response to these efforts [33]”. This highlights the interleaved behaviors of help-seeking by patients and families on the one hand, and the response of professionals and agencies on the other in generating a particular patient’s pathway into treatment. There is considerable information on a diverse set of barriers relevant to U.S. pathways, but the lack of consensus on measures and the multiplicity of factors limits straightforward application of available measures to a particular geographic area. Fortunately, STEP has collected relevant information over 6 years of recruiting from the local catchment that has included more than 600 formal inquiries and multiple informal consultations to families, clinics and area non-healthcare settings (e.g. churches, schools, mosques). This has allowed us to populate a heuristic model. While not exhaustive, it integrates salient elements of our local pathway to care.

We integrate these ideas in a modified version of the influential Goldberg-Huxley model [34] (Figure 1) to understand the interaction of both patient/caregiver factors and system factors relevant to DUP. The choices for sampling, ED implementation, measurement and analysis, described in the succeeding sections, derive from this model. While not exhaustive, the boxes correspond to the most common ‘levels’ or recognized sources of care in STEP’s target catchment (8 towns). The model conceives of these levels as not just sources of referral or delay but rather as ‘filters,’ hastening access to STEP for some kinds of patients while potentially delaying it for others. This phenomenon of filtering, whereby different levels of care may influence access in non-random ways, is exemplified by STEP’s experience of rapid (short-DUP) referrals of agitated, predominantly male patients from acute settings on the one hand, while also explaining a paradoxical finding reported in other settings: prior connection to outpatient care may actually delay entry to specialty FES [35]. Particular kinds of patients may proceed through particular ‘levels’ of care with unexpected speed or delay and this suggests the need to target, measure and analyze sources of DUP within the context of local pathways.

The story illustrates several salient contributors to DUP. The delayed recognition of the presence of an illness by the patient and his mother reflects a combination of factors including lack of awareness of the signs of mental illness and of available resources, denial, and fear of stigma - all of which delay effective help-seeking behavior that could have preempted the behavioral crisis and police intervention. The aversive experience of entering and receiving care under duress likely reduced the patient’s willingness to follow through on referrals to an FES. Many other combinations of the various levels are involved in the variety of pathways that contribute to the ‘demand’ and ‘supply’ components depicted in Figure 1. It is important to note that the demand and supply contributors to DUP often do not resolve in a linear fashion, but can result from a dynamic interplay of events. For example, a patient may enter an FES at the behest of a parent, with effective interruption of the DUP long before they can identify the presence of symptoms or the need for professional care. This perspective informs the pluralistic strategy of the campaign detailed below, which envisions diverse ways to interrupt DUP that seek to facilitate, but do not require, salutary changes in attitudes, beliefs or stigma.

The STEP-ED campaign will target both the lack of effective ‘demand’ for specialty care (dotted line) and effective ‘supply’ of such care (solid lines) in 3 principal ways: (1) a public Education Campaign (PEC), (2) outreach to and academic detailing of professionals (PO) to modify the filtering enacted at the various levels depicted in the model and (3) implementing Rapid Access to STEP (RAS) that will include a variety of performance improvement tactics to reduce the time between referral and admission to STEP.

### Aims and Hypotheses

This study seeks to test of the effectiveness of an early detection campaign in a policy-relevant U.S. setting, where relatively fragmented pathways to care magnify both the challenges and the potential public health impact. The presence of 2 similar, effective, geographically separated but collaborative FES programs (STEP and PREP^R^) presented an excellent opportunity to conduct such a test and thereby advance secondary prevention for psychotic illnesses in the U.S.

The guiding questions for this study are: can a U.S. adaptation of the TIPS approach to early detection substantially reduce DUP and improve outcomes beyond existing FES?

#### The primary aim is

To determine whether early detection intervention can reduce DUP in the US, as compared to usual detection. Early detection (ED) will be implemented in one US community (New Haven, CT), and usual detection efforts will continue in another (Boston, MA). DUP will be measured at admission to the corresponding services (STEP & PREP^R^) in each community, over one year before and throughout ED implementation. We hypothesize that DUP will be reduced significantly in the early detection site compared to the usual detection site.

#### The secondary aim is

To determine whether DUP reduction can augment the outcomes of established FES. We will measure symptoms, functioning and engagement with treatment at entry and over 1 year at each site. We hypothesize that the shorter DUP engendered by the ED campaign at one FES (STEP) will result in reduced distress and illness severity at entry and better 1 year outcomes and engagement at STEP vs. PREP^R^.

## Methods/Design

### Design rationale

Any effort to test the impact of an early detection strategy to reduce DUP and determine the subsequent impact on early outcomes, must confront specific biases [36] that are each addressed in the Procedures detailed below. First however, the overall rationale for the quasi-experimental design involving 2 sites is outlined:

### Primary aim

Any test of a DUP reduction strategy in a community has to consider 2 main sources of confounding. First, unexpected changes in either direction for DUP may occur over the life of this study (e.g. variation in healthcare access due to macroeconomic changes) that will imperil inferences from the sole use of a historical control to determine the impact of ED on DUP. The parallel control in this proposal (PREP^R^) ameliorates this concern by being carried out during the same period and allowing for careful measurement (see below) of these influences. In addition, the historical control design in New Haven (pre- and post-ED) also allows us to consider the effects of ED without the impact of unknown sources of heterogeneity in DUP across sites. The second source of confounding is preferential sampling from the larger target sample of new onset cases. For example, a correlation between ED and shorter DUP might merely reflect strategic success at diverting short DUP cases to STEP, while longer DUP cases remain untreated, or treated elsewhere, in the community. This is addressed by (a) our intensive media and targeted education campaign to facilitate representative recruitment from across the catchment and (b) the availability of a historical control at the STEP site, wherein DUP distributions available for years before ED implementation will allow pre-post comparisons to assess for differential skewing. Finally, (c) DUP will also be measured at a major community mental health center (the Hill Health Center, HHC, Connecticut) in the catchment area of the ED intervention for one year before and during the ED implementation. Specifically we will measure DUP for those who are not successfully referred to STEP. Three possibilities will be considered for this group: if DUP at HHC remains the same or falls, this would reassure us that ED had no effect or a salutary effect on help-seeking, even if not to STEP; while if the DUP rises for this group, it would raise concerns for biased sampling as described above. Notably, such skewed sampling did not occur in the TIPS project [37] and given the similar catchment based design, and the reality that few competing resources for early psychosis care are available in the STEP catchment, such skewing is unlikely to occur in STEP-ED.

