### Sampling

The early detection strategy (ED) will target all residents of a designated geographic catchment contiguous with the Connecticut Mental Health Center (CMHC) in which STEP is located. This includes the 8 towns of Bethany, Orange, Woodbridge, Hamden, New Haven, East Haven, West Haven and North Haven, with a total population of 323,285 (Census, 2010) and for which we estimate an annual incidence 40–70 cases of schizophrenia-spectrum disorders. The catchment was chosen based on feasibility of travel for care at STEP. The intensive approach to ascertainment of new onset cases from across the catchment will include public messaging and targeted outreach to all major treatment centers. Also measurement of DUP will be undertaken at one other major community mental health center that draws from this catchment zone. At this community ‘sentinel’ site, in addition to the usual outreach, clinical records will be reviewed on a regular basis to determine the prognostic profile and DUP of patients who were not successfully referred to STEP for initiation of treatment. The control site, PREP^R^ is based in the Jamaica Plains area of Boston and while it draws from a much larger metropolitan population of more than 4 million (Census 2010), the demographic and prognostic profile of usual recruits over the past 5 years have been broadly comparable to that of STEP (see section *Choice of Control site* below).

The focus of early intervention after the onset of a psychosis is to improve the outcomes of individuals with schizophrenia-spectrum disorders. The reality, embraced by all exemplar early intervention programs, is that an accurate diagnosis is often difficult to make at the time of symptom onset [42]. Thus a ‘first-episode’ psychosis sample will necessarily include patients who will, on longitudinal follow-up, turn out to have less severe illnesses such as major depression with psychotic features, brief psychotic disorder or bipolar disorder (with psychotic features). The study population is thus expected to be diagnostically heterogeneous in the service of identifying, with as much sensitivity as possible, those who are likely to develop chronic psychotic illnesses.

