### Measurement

#### Choice of measures

##### Measuring DUP

Consensus on a valid measure of DUP has been elusive. There are difficulties in reliably determining the onset of a private mental event and also reasonable differences in opinion on what constitutes meaningful offset, or when treatment can be considered to have begun [50]. We will collect detailed onset data for a variety of psychotic phenomena and treatment events in order to allow comparison with other study cohorts. For the purposes of planning our recruitment, we chose to define onset of DUP per the threshold criteria for positive or disorganized symptoms of psychosis in the Symptom Onset Scale (SOS) [51]. The SOS was chosen for several reasons: (a) it is comprehensive, rating the severity and dating the onset of 16 general prodromal, positive, negative, and disorganization symptoms, as well as recording clinician, family, and patient global ratings of onset of illness; (b) it has good reliability; [51] and (c) both sites in New Haven and Boston have had considerable experience with this instrument over ≥5 years.

With respect to offset, we conceptualize DUP1 as ending on the date of initiation of antipsychotic medication treatment targeting psychosis. Given evidence that these symptoms can respond within a few days of antipsychotic medication treatment, [52] we chose *initiation* over more stringent criteria for *adequacy* of medication treatment proposed by others (e.g. adequate dose with 75% adherence for at least 4 weeks [53]). This will allow us to disentangle timing from quality of treatment (in which one might include the receipt of an adequate antipsychotic trial). Assessors will collect an inventory of every medication prescribed to the patient, including dates and minimal adherence to help determine the offset of DUP1. We define DUP2 as the date of admission to an FES (STEP/PREP^R^ or other comparable services in the Boston area). This approach allows us to evaluate the differential impact of the campaign on various definitions of offset [53] and subsequently, on 1 year outcomes.

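### Unchanged or lower DUP among non-referred Hill Health Center patients cannot rule out selective sampling, and a rise cannot establish it

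*Protocol article*

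**What the plan says.** In the Primary aim subsection of the Design rationale, the protocol article names preferential sampling as the second of two main sources of confounding. An association of early detection with a shorter wait is said to be open to another explanation: it "might merely reflect strategic success at diverting short DUP cases to STEP, while longer DUP cases remain untreated, or treated elsewhere, in the community".

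Three safeguards follow: the catchment-wide campaign, STEP's historical DUP distributions, and measurement of DUP at HHC "in the catchment area of the ED intervention for one year before and during the ED implementation". The HHC group is restricted: "Specifically we will measure DUP for those who are not successfully referred to STEP". The result is to be read as follows: "if DUP at HHC remains the same or falls, this would reassure us that ED had no effect or a salutary effect on help-seeking". The opposite result is covered too: "while if the DUP rises for this group, it would raise concerns for biased sampling as described above".

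The Sampling section adds that the HHC data come from regular review of clinical records. Neither section says how many patients are expected there or which DUP is meant. Under Measuring DUP there are two versions. DUP1 ends when antipsychotic medication is started. For the other, "We define DUP2 as the date of admission to an FES". DUP2 is the primary outcome (Choice of primary and secondary outcomes).

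**The concern.** The reading rule does not match the threat it is meant to detect. The threat has two branches: long-DUP cases are treated elsewhere, or they are not treated at all. A record review at a treatment center can see only the first. Stable or falling DUP at HHC is therefore what one would expect both when there is no selection and when the missed cases never reach care.

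The other side of the rule is also open to more than one explanation. The HHC group is defined by not being referred to STEP, and changing referral is what the professional outreach sets out to do. The make-up of the group can therefore shift between periods without any change in how long patients wait.

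At stake is how a positive primary result would be defended. The trial is not randomised. STEP's own historical distribution shifts under both a true reduction and selection, so it cannot separate them alone. The DUP estimated for refusers covers only people who were already referred. HHC is the planned look at catchment patients outside the STEP referral stream, so its reading would carry weight in the interpretation.

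**Working it through.** **Inputs from the protocol article (Sample size and power).** STEP log-DUP mean 1.6, SD 1.3; planned fall to 0.8; pre-campaign n 66 (PREP) and 133 (STEP); post-campaign n 66 and 102; alpha 0.05, taken as two-sided; stated power 81%. Routing of patients and HHC counts are not given and are assumed below.

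**Stated power.** SE = 1.3 × √(1/66 + 1/133 + 1/66 + 1/102) = 0.2837. Power = Φ(0.8/0.2837 − 1.96) = Φ(0.86) = 0.805. This agrees with the stated 81%. The HHC check has no stated power figure and does not enter this test.

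**Can the rule reassure when selection produced the result?** Take log-DUP as N(1.6, 1.3), change nobody's DUP, and let cases above 2.0 (e^2.0 = 7.4 months) stay untreated during the campaign.
- z = (2.0 − 1.6)/1.3 = 0.308; share above = 1 − Φ(0.308) = 0.38.
- Mean of those still seen = 1.6 − 1.3 × φ(0.308)/Φ(0.308) = 1.6 − 1.3 × 0.3805/0.6208 = 0.80.
- STEP falls from 1.6 to 0.80, the full planned effect. HHC, drawing on the same treated pool, also falls to 0.80. The rule reassures.

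A milder version keeps 60% of cases at STEP, 20% at HHC (drawn at random) and 20% untreated, with long-DUP cases increasingly likely to be untreated (logistic slope 0.5 to 4). STEP then falls to between 1.40 and 1.08 while HHC stays at 1.60. The rule again reassures.

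**Can HHC DUP rise although catchment DUP truly fell?** HHC is taken as unselected (1.6) before the campaign.
- Every case's log-DUP falls by 0.8, short-DUP cases are referred preferentially, and HHC keeps 10% of treated cases. The HHC mean is 1.54, 2.09, 2.44 and 2.65 at logistic slopes 0.5, 1, 1.5 and 2. With HHC keeping 25%, it is 1.39, 1.79, 2.02 and 2.16. A rise above 1.6 appears at slopes of 1 or more, but not at 0.5.
- The campaign brings long-hidden cases (assumed log-DUP 3.2) to HHC. If other HHC cases are unchanged, a 20% share gives 0.8 × 1.6 + 0.2 × 3.2 = 1.92. If the others improve to 0.8, a rise needs 0.8(1 − k) + 3.2k > 1.6, so a share k above one third; at 40% the mean is 1.76.

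**How informative is no change?** Assume 5, 10 or 20 HHC patients a year, one year before and three during, SD 1.3. The 95% half-width is 1.96 × 1.3 × √(1/n + 1/(3n)):
- 5 a year: 1.32 log units (a factor of 3.7); power for a 0.8 rise 22%.
- 10 a year: 0.93 (2.5); power 39%.
- 20 a year: 0.66 (1.9); power 66%.

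**Which DUP?** DUP2 has no end date for an HHC patient who never enters a first-episode service. DUP1 has one once an antipsychotic is started.

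**The case against.** The protocol speaks of reassurance and concern, not of a formal decision. HHC is the third of three listed safeguards, refusers' DUP is estimated as well, and none of this enters the primary test. All of that stands and limits the consequence.

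A reader might infer more than the documents support, in four ways.

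- *That the rule sounds an alarm whenever the campaign works.* It does so only under strong assumptions: marked preferential referral of short-DUP cases, or a large inflow of hidden ones. In the referral scenario some selection did occur: with HHC keeping 10%, STEP's mean is 0.59 to 0.71 against a catchment mean of 0.80, so concern is partly fair. If short-DUP cases simply move from HHC to STEP and nobody's DUP changes, the rise at HHC is a correct signal of the bias the protocol names.
- *That DUP is undefined for HHC patients.* The text says only DUP, and DUP1 does not require entry to a first-episode service. The version is unnamed; only DUP2 cannot be computed.
- *That the HHC group is known to be very small.* No count is given. Subtracting STEP's 34 enrollees from the catchment figure, where "we estimate an annual incidence 40–70 cases" of schizophrenia-spectrum disorders, mixes annual incidence with a consented, diagnostically mixed sample whose onset may be up to three years old.
- *That HHC is the only concurrent check in the catchment.* The refuser estimates are another, though confined to people already referred.

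**Conclusion.** The reassurance side of the HHC rule does not hold. Unchanged or lower DUP among non-referred HHC patients is compatible with selection large enough to produce the entire planned 0.8 fall at STEP, because untreated cases leave no HHC record. The truncation at 2.0 is a deliberately sharp illustration on the protocol's own distribution; the graded versions give STEP falls of 0.20 to 0.52 with HHC flat. A rise is ambiguous rather than wrong, and that part rests on assumed routing. The claim about precision rests on assumed HHC counts and on borrowing STEP's SD; it shows that no change may be uninformative, not that it will be. The unnamed DUP version is a real but smaller gap. The point concerns how a supportive check is interpreted. It should be corrected, but it does not undermine the primary interaction test or its stated power.

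**What to change.** In the Primary aim and Sampling sections:

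1. State that the HHC check uses DUP1.
2. Extend the planned record review to all new-onset HHC cases, referred or not.
3. Compare the pooled STEP and HHC DUP1 distribution before and during the campaign, with a confidence interval. Pooling removes the dependence on who is referred from HHC to STEP.
4. Report case counts by period as a rough guide to untreated cases. In the truncation example, treated cases would drop by 38% if all had reached care before; in the graded example the count would not change, so this is only a partial safeguard.
5. Replace the present reading with a statement that DUP in the non-referred group alone can neither exclude nor establish selection.

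The cost is protocol wording and modest extra chart abstraction, with no change to the campaign, the sample size or the primary analysis. Two limits remain: the check bears on DUP1 rather than directly on DUP2, and it still cannot fully see untreated cases.
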